**3rd trimester**

**Delivery**

**Recruitment**

**4 wks**

**12 weeks**

Baseline visit

mHealth *Fit After Baby* program

Text4Baby

**Randomization**

**Study visit measures: weight, height, blood pressure, waist circumference, glucose, HbA1c, insulin, adiponectin, lipids, hsCRP, physical activity, depression, hCG, optional stool sample**

**Flow of *Fit After Baby* RCT**

**12 months**

Final visit

**6 months**

6 month visit

**Measures:** Body weight and height: We will determine weight, measured twice wearing light clothing. We will obtain pre-pregnancy weight by self-report. Others have shown a high correlation (R=0.99) between self-reported and clinically measured pre-pregnancy weight.^[[45]](#endnote-45)^ We will measure height and use kg/m^2^ to determine BMI. 2) Demographics: We will collect age, self-reported ethnicity and race, working status, parity, family history of diabetes and cardiovascular disease, prior personal history of pregnancy complications, education level, marital status, number/ages of children living at home, and number of other household members. 3) Pregnancy test: We will obtain urine for rapid determination of hCG at the follow-up visit at 6 and 12 months postpartum. If the test is positive the participant will be referred to her clinician for confirmatory testing. We will not do hCG tests at the baseline visit, since many women will still have positive levels from pregnancy. If a woman is determined to be pregnant during the study year they will be censored at that timepoint. We do not anticipate any harm to participation even if a woman were to become pregnant during the study. 4) Waist Circumference: Per NHANES methodology.^[[46]](#endnote-46)^ 5) Blood pressure: Determined twice, five minutes apart in the seated position after 15 minutes of rest. Values will be averaged. 6) Biomarkers: HbA1c, hsCRP, adiponectin and fasting glucose, insulin, and lipids. 7) Potential mediators: Diet will be assessed by 2005 Block FFQ, administered online during the study visit. Physical activity will be assessed using an adapted Pregnancy Physical Activity Questionnaire (PPAQ).^[[47]](#endnote-47)^ Breastfeeding intensity and frequency will be assessed through a short questionnaire. 8) Potential moderators: Postpartum depression (PPD) will be assessed using the Edinburgh Postnatal Depression Scale (EPDS).^[[48]](#endnote-48)^ Women found to have PPD (defined as an EPDS score ≥12) will be assessed by a study clinician and offered a referral to services. They will be allowed to continue in the study. Any woman screening in for self-harm or harm to others will be immediately referred for mental health evaluation. We will assess appetite and sleep using real-time visual analog scales in the app. 9) Satisfaction: Likert scale for satisfaction and willingness to recommend to a friend.

| **Table 3: Measurements**  **Variable** | **Day 1, 2, or 3 pp** | **Visit 1**  **(6 wks pp)** | **Visit 2**  **(6 months pp)** | **Visit 3**  **(12 months pp)** |
| --- | --- | --- | --- | --- |
| Demographics Questionnaire (Based on Behavioral Risk Surveillance System (BRFSS) |  | X |  |  |
| Height |  | X |  |  |
| Medical History Update |  | X | X | X |
| Urine hcg* |  |  | X | X |
| **Clinical Outcomes** | | | | |
| Weight |  | X | X | X |
| Waist circumference |  | X | X | X |
| Heart Rate |  | X | X | X |
| Blood Pressure |  | X | X | X |
| Fasting lipid profile |  | X | X | X |
| HbA1c |  | X | X | X |
| TSH |  | X | X | X |
| OGTT (only for GDM women) |  | X |  |  |
| Fasting glucose |  | X | X | X |
| Fasting insulin |  | X | X | X |
| Adiponectin |  | X | X | X |
| hsCRP |  | X | X | X |
| **Behavioral Outcomes** | | | | |
| Adapted Pregnancy Physical Activity Questionnaire (PPAQ) |  | X | X | X |
| 2005 Block FFQ |  | X | X | X |
| Breastfeeding Questionnaire |  | X | X | X |
| **Mediating Variables** | | | | |
| Social Support for Eating |  | X | X | X |
| Social Support for Exercise |  | X | X | X |
| Self Efficacy Survey for Diet and Exercise Behaviors |  | X | X | X |
| Readiness to Change Questionnaire |  | X | X | X |
| Perceived Stress Scale |  | X | X | X |
| Edinburgh Postnatal Depression Scale (EPDS) |  | X | X | X |
| Sleep Questionnaire |  | X | X | X |
| Satisfaction |  | X | X | X |

*NOTE: Subjects will not take a urine hcg test at 6 weeks because the hcg would be expected to be elevated from pregnancy and would not be able to identify a new pregnancy. All subjects will take a pregnancy test at every subsequent study visit. In addition, if subject reports new amenorrhea, the subject will be asked to come in for a pregnancy test. If results indicate exclusionary condition such as pregnancy, subject will be removed from study and referred for appropriate clinical follow-up care. These subjects will be excluded as they would affect study data and because these conditions may require different care. If a subject is diagnosed with diabetes at any visit, we will ask their permission to continue to follow them. Permission will be requested to obtain medical records for the pregnancy to look at recurrence of pregnancy complications in both groups.

*NOTE: Measures will be taken to review subject data and diagnose diabetes according to American Diabetes Association (ADA) guidelines. The following values at the specified timepoints throughout the study year indicate that the subject will need to repeat the abnormal test to confirm the diagnosis of diabetes:

• At the 6-week visit, if the subject has a fasting glucose value >126 or a 2-hour OGTT glucose value >200. The HbA1c value collected at the 6-week visit is exploratory and is not clinically used to diagnose diabetes at 6-weeks, given that the result will be affected by hyperglycemia during pregnancy.

• At the 6-month and 12-month visits, if the subject has a fasting glucose value > 126 or a 2-hour OGTT glucose value >200 or if the HbA1c value is >7.0. For HbA1C values between 6.5 and 7.0, we will use the values from the OGTT as the standard for making a diagnosis for DM.

If two of the subject’s initial clinical tests exceed these values, they will be diagnosed with diabetes at that timepoint. If one of the subject’s initial clinical tests exceeds these values we will schedule a repeat fasting glucose, OGTT, or HbA1c. If the subject’s repeat test result exceeds these values, the subject will be diagnosed with diabetes. Subjects diagnosed with diabetes at the 6 week visit will be excluded from the study. If a subject is diagnosed with diabetes at any visit other than the 6 week visit, we will continue to follow them. This is to ensure that we can collect data on all randomized subjects, including body weight which is the primary outcome of the study. We will assist all subjects diagnosed with diabetes with a referral to an appropriate provider to manage their condition.

Validated Questionnaires

1. Demographics Questionnaire (Based on the Behavioral Risk Factor Surveillance System (BRFSS). http://hmcrc.srph.tamhsc.edu/Measures/BRFSS%20Demographic.pdf

2. Social Support for Eating Habits Survey - Sallis. http://www-rohan.sdsu.edu/faculty/sallis/socialsupport-eatinghabits.pdf.

3. Social Support for Physical Activity - Sallis. http://www-rohan.sdsu.edu/faculty/sallis/socialsupport-exercise.pdf.

4. Self Efficacy Survey for Diet and Exercise Behaviors. http://www-rohan.sdsu.edu/faculty/sallis/self-efficacy-coverandexercise.pdf

5. Perceived Stress Scale. http://www.macses.ucsf.edu/Research/Psychosocial/notebook/PSS10.html.

6. Edinburgh Post-Partum Depression Scale (EPDS)* http://www.fresno.ucsf.edu/pediatrics/downloads/edinburghscale.pdf.

7. 2005 Block FFQ

8. Pregnancy Physical Activity Questionnaire (PPAQ) http://www.ipaq.ki.se/.

9. Breastfeeding

10. Readiness to Change Questionnaire

http://www.rrh.org.au/publishedarticles/article_print_802.pdf

*NOTE: The Edinburgh Depression screen will be scored before the participant completes the study visit. A score ≥12 on the Edinburgh Depression Screen will prompt evaluation by a clinician, consistent with the clinical practice of the outpatient obstetric practices and the cutoffs published in the most current literature.^[[49]](#endnote-49)^ Per usual clinical care, any participant deemed acutely suicidal will be sent to the ED for emergent evaluation by psychiatry. Participants deemed to be at risk for depression, but not acutely suicidal, will be referred for further care.

For this study, these questionnaires will be organized according to topic into 4 groups and combined into one single computer administered study questionnaire to make them readable and user-friendly. To facilitate this grouping, the questionnaires have undergone some format changes and some questions have been removed.

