Upon signing the consent form and enrolling in this research study, all women will be scheduled for their first of 3 study visits approximately 6 weeks postpartum. The consent form will include language to allow study staff access to the medical record information to confirm medical diagnoses by the inclusion criteria stated above. Subjects who do not have medical conditions as defined by the inclusion criteria stated above documented in their medical records will not be eligible to continue in the study. If a subject becomes pregnant during the course of the study, she will be asked to be followed during the pregnancy to determine occurrence of pregnancy complications and gestational weight gain.

Study Visits

At study visits, all women will be assessed for clinical outcomes, behavioral outcomes, mediating variables, and moderating variables (see table 3). Clinically relevant labs (pregnancy tests, OGTT, fasting glucose, HbA1c, TSH, LDL, triglycerides) will be reviewed when results are available. All subjects will complete approximately 45 minutes of questionnaires at study visits.

In accordance with ADA recommendations and UCH standard of care guidelines for postpartum diabetes screening for patients with prior GDM, which suggest 6 week postpartum glycemic status check via oral glucose tolerance test (OGTT), all enrolled subjects with a history of GDM will be offered an OGTT. Study staff will schedule this visit and with the subject’s permission, share OGTT results with subject’s pregnancy care provider (MD or CNM), thereby eliminating the scheduling of duplicate lab appointments. We anticipate this collaboration with OB caregivers will be welcomed, as published data demonstrate clinicians have a difficult time getting these women in for their 6 week postpartum OGTT – less than 50% of women had a 6 week postpartum OGTT.^[[42]](#endnote-42)^

All subjects will be instructed to arrive fasting to study visits, i.e. nothing except water for 10 hours prior to study visit. At study visits up to 50 cc of blood will be drawn, including fasting bloods and optional blood for storage.

During the first study visit, all enrolled subjects will be randomized using previously described permuted block scheme to either control or intervention arm.

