**Statistical Analysis**: The analysis for the primary outcomes will be intent-to-treat, using longitudinal mixed methods to account for loss to follow-up and censored participants. Due to the longitudinal nature of this study, we will assess the change in weight from the 6-week study visit to weight at 6 and 12 months by a mixed model analysis with an exchangeable correlation structure and adjustment for weight gain during pregnancy, and breastfeeding (a mediating effect). Within this model, we can further assess differences in weight between various time points by contrasts. We will also compare the delta weight prepregnancy to 6 and 12 months postpartum in the intervention group to the control group using a multivariate regression model, adjusting for age and race. Secondary clinical outcomes will be compared between groups by a generalized linear mixed model analysis, similar to the primary outcome analysis. When necessary, adjustment for multiple comparisons will be made. We will assess reach, effectiveness, and adoption per the RE-AIM model to prepare for a pragmatic trial (Table 2). We will use content-based analysis on focus group data to assess perceived barriers and facilitators to success of the intervention.

**Anticipated results**: Primary outcome: We expect that women who participate in the *Fit After Baby* program will demonstrate increased weight loss in the postpartum year vs. the Text4Baby control group. Secondary outcomes**:** We expect an improvement in cardiometabolic risk factors among women randomized to the Fit After Baby program. We anticipate that increased engagement and satisfaction will be associated with increased weight loss. We expect that decreased caloric intake relative to expenditure and increased physical activity will help to mediate weight loss. We anticipate that postpartum depression may interfere with weight loss as it will decrease engagement with the program, and appetite and sleep may also moderate weight loss.

| **Table 2: Relevant RE-AIM Outcomes** | **Measures/Data Source** | |
| --- | --- | --- |
| **REACH** | | |
| 1) Proportion of approached women agreeing to participate  2) Proportion of recruited women initiating program | | 1) Recruitment data  2) App usage data |
| **EFFECTIVENESS** | | |

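### The note under Table 3 removes randomised women who become pregnant, and 6-week diabetes exclusions can follow allocation; both conflict with the intent-to-treat statement and with other sections

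*Protocol*

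**What the plan says.** **Pregnancy during the study.**

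- Note under Table 3: "If results indicate exclusionary condition such as pregnancy, subject will be removed from study and referred for appropriate clinical follow-up care". The reason follows: "These subjects will be excluded as they would affect study data and because these conditions may require different care". The note ends by seeking permission to obtain records of the new pregnancy.
- Measures, item 3 (Pregnancy test): "If a woman is determined to be pregnant during the study year they will be censored at that timepoint".
- Section 5.6, Medical Record Review: "she will be asked to be followed during the pregnancy to determine occurrence of pregnancy complications and gestational weight gain".

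**Diabetes found at the first visit.**

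- The diabetes note after Table 3, and again item 1 (Glucose, HbA1c) under Outcomes monitoring: "Subjects diagnosed with diabetes at the 6 week visit will be excluded from the study". Both places schedule a repeat test when a single initial test is abnormal. Both keep women diagnosed at later visits, giving as the reason the wish to have data, body weight included, on everyone randomised.
- Note under Table 3: "If a subject is diagnosed with diabetes at any visit, we will ask their permission to continue to follow them".

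**Allocation and analysis.**

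- Section 5.6, Study Visits: "During the first study visit, all enrolled subjects will be randomized using previously described permuted block scheme". Section 5.5 likewise places randomisation at the first visit. Section 5.6 has laboratory results reviewed as they become available.
- Statistical Analysis: "The analysis for the primary outcomes will be intent-to-treat, using longitudinal mixed methods to account for loss to follow-up and censored participants".

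**The concern.** An intent-to-treat comparison keeps each randomised woman in the arm to which she was assigned. Pregnancy during the study year arises after allocation. Diabetes present at 6 weeks is a baseline condition, but under this protocol its diagnosis can also come after allocation. A rule that takes such women out of the analysis because of their effect on the data departs from the stated principle.

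Two things are at stake. First, the analysis population is not fixed: people following different sections could build different datasets from the same trial. Second, allocation is open. One arm has an app, a coach, a Fitbit and a scale, while the other has text messages. If attendance for a repeat glucose test or reporting of amenorrhoea differed by arm, and the women removed differed in weight course from those who stayed, the comparison would be biased. The protocol does not show that this will happen, but its wording leaves room for it.

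**Working it through.** This is mainly a comparison of sections. The one relevant figure, the planned power, is reproduced to show why it does not measure the problem.

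**1. Pregnancy.** Take a woman weighed at baseline and at 6 months, who conceives at month 9 and tests positive at the 12-month visit.

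- Under Measures item 3 with Statistical Analysis, she is censored at detection. Her baseline and 6-month weights stay in the mixed model and her 12-month weight is not used.
- Under the Table 3 note read narrowly, her participation stops and her earlier weights stay. The dataset is the same as above.
- Under the Table 3 note read broadly, she is excluded because she would affect the data. She contributes nothing, and a valid 6-month weight is lost.
- Section 5.6 asks to follow her for complications and gestational weight gain. Those are outcomes of the new pregnancy, so this can coexist with censoring her study weight.

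The conflict is therefore between removal or exclusion on one side and censoring on the other. It affects the 6-month part of the primary outcome as well as the 12-month part.

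**2. Diabetes at 6 weeks.**

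- Randomisation takes place during visit 1 (sections 5.5 and 5.6).
- The diagnosis uses fasting glucose and, for women with prior gestational diabetes, an OGTT from that visit.
- One abnormal result leads to a scheduled repeat, which can fall after the visit.
- No section holds allocation until results or repeats are available.

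So a woman can be allocated, told her arm, and excluded later. The Table 3 note instead asks permission to keep following a woman diagnosed at any visit, which includes visit 1. Diabetes found at 6 or 12 months is not affected, since the diabetes note and the monitoring section both retain those women.

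**3. Planned power.** Inputs from the power paragraph are 54 and 27 women, a difference of 4.2 kg and an SD of 5.7 kg. Two-sided alpha of 0.05 is an assumption, as the protocol does not state it.

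- Standard error = 5.7 × √(1/54 + 1/27) = 5.7 × 0.2357 = 1.3435 kg.
- Noncentrality = 4.2 / 1.3435 = 3.126, with 79 degrees of freedom.
- Power from the noncentral t distribution = 87.0%, which matches the stated figure of at least 87%.

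If some of the 81 were lost, the same formula gives:

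- 2% lost (53 and 26): 86.0%
- 10% lost (49 and 24): 83.1%
- 20% lost (43 and 22): 79.0%

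These percentages lost are assumptions. The protocol gives no rate of pregnancy or of diabetes at 6 weeks, and the 81 are described as participants with one-year data out of 140 consented, so they may already be net of such losses. In that case power is unchanged.

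The fix would also recover little of any loss from pregnancy: a woman pregnant by 12 months supplies no usable 12-month weight under either rule.

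**The case against.** The strongest reply on pregnancy is that the analysis rule is already there. Measures item 3 censors the woman and the Statistical Analysis section names censored participants, so weights before pregnancy stay in. On that view the Table 3 note describes only the end of participation. This is a reasonable reading, and it is why the loss of earlier weights cannot be stated as fact: no section says that data already collected are discarded. What remains is that the note's first reason concerns the study data and not only the woman's care, and that it uses the language of exclusion where the other sections use censoring.

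On diabetes, the reply is that the condition was present at baseline and section 5.4 already excludes known diabetes. If exclusion rested only on visit 1 samples and was decided without knowledge of arm, the risk of bias would be small. That is correct, but the protocol requires neither condition. Nor does it state the order of laboratory results and randomisation within the visit, so exclusion after allocation is possible rather than certain.

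Differential detection of pregnancy is also limited, because urine hCG is scheduled for both arms at 6 and 12 months. Only the additional test prompted by reported amenorrhoea depends on the participant. Unequal removal by arm is not in itself bias.

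A reader might infer three stronger points that the documents do not support: that earlier weights are certainly dropped, that there are three incompatible pregnancy rules, and that power falls by a known amount. The first is only one reading of the note. The second overlooks that follow-up of the new pregnancy is compatible with censoring. The third rests on an assumed rate.

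**Conclusion.** The protocol is inconsistent on two events that decide who is analysed. For pregnancy, the Table 3 note conflicts with Measures item 3 and with the intent-to-treat mixed model. For diabetes at the 6-week visit, an exclusion that can follow open allocation conflicts with the intent-to-treat statement, with the stated aim of having weight on everyone randomised, and with the Table 3 note on diagnosis at any visit. Followed as written, the plan permits post-randomisation exclusions.

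The size cannot be given. The number of women affected is unknown, and neither the direction nor the existence of a bias is established. With 27 controls planned at one year, each control woman is 1/27 = 3.7% of her arm, so even a few removals would be visible. The conclusion rests on the wording of the sections and needs no assumption about rates.

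**What to change.** Reconcile the Table 3 note, Measures item 3, the diabetes note and the Outcomes monitoring section, and align section 5.6 with them, so that analysis membership follows the intent-to-treat statement:

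- State that stopping study participation does not remove a randomised woman from the analysis set.
- For pregnancy, state that all weights before the timepoint of detection stay in the mixed model, that later weights are treated as censored, and that pregnancies are reported by arm.
- For diabetes at 6 weeks, either settle glucose eligibility, including any repeat test, before allocation, or keep women already randomised in the weight analysis.

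The sponsor must also reconcile the sections on clinical handling and continued participation of these women; no clinical rule is proposed here. Under the second diabetes option, that decision determines whether a retained woman supplies follow-up weights or only a baseline weight.

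The cost is protocol wording. If eligibility is settled first, there is also a short delay between the baseline visit and randomisation.

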10. Taking certain prescription medications including long-term high dose glucocorticoids, atypical antipsychotics associated with weight gain (such as respirdal (respiradone), clozapine (klozaril), olanzapine (zyprexa), quetiapine (seroquel), etc.)) or weight loss medications including prescription (Qsymia, phentermine, topiramate, Belviq, Contrave, Saxenda, Orlistat), or non-prescription (Alli) medications;
11. Taking metformin or other medications known to affect glucose metabolism during the postpartum period;
12. Other active medical problems detected by examination or laboratory testing, at the discretion of the physician;
13. During the first trimester, any fasting blood glucose > 126 mg/dl, any HbA1c at or above 6.5%, or any plasma glucose >200 mg/dl.

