For participants with a recent history of GDM who complete an oral glucose tolerance test: At the 6-week visit, if the subject has a fasting glucose value >126 or a 2-hour OGTT glucose value >200. The HbA1c value collected at the 6-week visit is exploratory and is not clinically used to diagnose diabetes at 6-weeks, given that the result will be affected by hyperglycemia during pregnancy.

For all other participants (who will not complete an OGTT):
At the 6 week visit, if the subject has a fasting glucose value > 126.

• At the 6-month and 12-month visits, if the subject has a fasting glucose value > 126 or if the HbA1c value is ≥6.5.

If two of the subject’s initial clinical tests exceed these values, they will be diagnosed with diabetes at that timepoint. If one of the subject’s initial clinical tests exceeds these values we will schedule a repeat fasting glucose, OGTT, or HbA1c. If the subject’s repeat test result exceeds these values, the subject will be diagnosed with diabetes. Subjects diagnosed with diabetes at the 6 week visit will be excluded from the study. If a subject is diagnosed with diabetes at any visit other than the 6 week visit, we will continue to follow them. This is to ensure that we can collect data on all randomized subjects, including body weight which is the primary outcome of the study. We will assist all subjects diagnosed with diabetes with a referral to an appropriate provider to manage their condition.

2. Fasting lipid profile:

Based on the 2013 ACC/AHA blood cholesterol guideline statins should be prescribed in patients without clinical atherosclerotic cardiovascular disease with a LDL-C above or equal to 190 mg/dL, if a subject has a LDL-C above 190mg/dL, the study physician will call the participant to let her know that her cholesterol level was elevated and that she should contact her PCP. If a subject has a fasting TG level above 800 mg/dL, the study physicianwill call the participant to let her know that her triglyceride level was elevated and that she should contact her PCP.

3. TSH: If a participant has a TSH out of the normal range at any timepoint she will be contacted and advised to contact her PCP.

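### Two conflicting HbA1c rules for diagnosing diabetes at 6 and 12 months: above 7.0 in the Table 3 notes, 6.5 or higher under Outcomes monitoring

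*Protocol*

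**What the plan says.** Two parts of the protocol set out which laboratory values at 6 and 12 months require a repeat test to confirm diabetes.

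- **Second note under Table 3 (section 5.6).** A fasting glucose above 126 is flagged, "or a 2-hour OGTT glucose value >200 or if the HbA1c value is >7.0". The next sentence covers the range below that limit: "For HbA1C values between 6.5 and 7.0, we will use the values from the OGTT as the standard" for the diagnosis.
- **Section 6.1, Outcomes monitoring, item 1 (Glucose, HbA1c).** At the same two visits a woman is flagged "if the subject has a fasting glucose value > 126 or if the HbA1c value is ≥6.5". No OGTT criterion is given for these visits.

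The rest of the algorithm is the same in both. Two initial tests beyond the limits make the diagnosis at that visit. If only one is beyond, "we will schedule a repeat fasting glucose, OGTT, or HbA1c", and if the "repeat test result exceeds these values, the subject will be diagnosed with diabetes". Both parts cite the ADA guidelines as their basis.

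Three other places bear on the point. Table 3 has HbA1c and fasting glucose at all three visits, but the row "OGTT (only for GDM women" is marked at visit 1 only. Section 5.6 says that "all enrolled subjects with a history of GDM will be offered an OGTT", in connection with the 6-week check. Exclusion criterion 13 in section 5.4 uses, for the first trimester, "any HbA1c at or above 6.5%, or any plasma glucose >200 mg/dl".

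**The concern.** The two rules serve the same purpose at the same visits, and they disagree over the whole HbA1c range from 6.5 to 7.0. The protocol does not say which prevails. The shared reference to ADA guidelines does not settle it, because both written limits claim that basis.

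The tie-break in the Table 3 note is also incomplete. It relies on OGTT values but does not order the test. Its repeat-test clause applies only when an initial result exceeds a listed value, and an isolated HbA1c of 6.5 to 7.0 does not exceed 7.0. Women without GDM are described in section 6.1 as not completing an OGTT at all.

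What is at stake is participant care. The diagnosis triggers the referral that the protocol promises, and section 6.1 names earlier care after a study diagnosis as a possible benefit. Two staff members following two pages could handle the same result differently.

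**Working it through.** The protocol gives no figure to reproduce here, so the check applies both rules to the same results.

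**Inputs**

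- Rule T (note under Table 3): fasting glucose (FG) above 126; HbA1c above 7.0; HbA1c 6.5 to 7.0 decided by OGTT, with a 2-hour limit above 200.
- Rule M (Outcomes monitoring): FG above 126; HbA1c 6.5 or higher.
- Both: no test beyond the limits, no further test; one, a further test; two, diagnosed at the visit.

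**Count of tests beyond the limits**

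- n(T) = [FG > 126] + [HbA1c > 7.0]
- n(M) = [FG > 126] + [HbA1c ≥ 6.5]

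The OGTT sentence in rule T can be read in two ways. Under reading A it implies that an OGTT is obtained for HbA1c 6.5 to 7.0, so the action there is at least a further test. Under reading B nothing is ordered unless n(T) is at least 1.

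**Action at the visit**, with one illustrative value for each range:

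| HbA1c | FG | n(T) | n(M) | Rule T, reading A | Rule T, reading B | Rule M |
|---|---|---|---|---|---|---|
| 6.3 | 110 | 0 | 0 | none | none | none |
| 6.3 | 130 | 1 | 1 | further test | further test | further test |
| 6.7 | 110 | 0 | 1 | further test | none | further test |
| 6.7 | 130 | 1 | 2 | further test | further test | diagnosed |
| 7.2 | 110 | 1 | 1 | further test | further test | further test |
| 7.2 | 130 | 2 | 2 | diagnosed | diagnosed | diagnosed |

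The action differs in 1 of 6 combinations under reading A (HbA1c 6.7, FG 130) and in 2 of 6 under reading B (also HbA1c 6.7, FG 110).

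**Final diagnosis for HbA1c 6.7 and FG 110, reading A.** Rule T lets the OGTT decide. Rule M allows a repeat FG, OGTT or HbA1c. If the repeat is an HbA1c:

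| 2-hour OGTT | Repeat HbA1c | Rule T | Rule M |
|---|---|---|---|
| 160 | 6.3 | no | no |
| 160 | 6.7 | no | diabetes |
| 210 | 6.3 | diabetes | no |
| 210 | 6.7 | diabetes | diabetes |

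The final diagnosis differs in 2 of 4 result pairs. If rule M's repeat is an OGTT judged at 200, both rules use the same result and none of the 4 differs.

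**A related gap.** Rule M permits an OGTT as the repeat test and compares it with the listed values, but Outcomes monitoring gives the 2-hour limit of 200 only for the 6-week visit.

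**The case against.** **Layout of Outcomes monitoring.** The 6- and 12-month bullet stands below a line addressed to participants who will not complete an OGTT. Read strictly, the 6.5 limit covers only those women. This narrows the conflict but does not remove it: the Table 3 note makes no such split, so women without an OGTT still fall under both limits. They are also the group for whom an OGTT tie-break is least workable. On this reading, Outcomes monitoring gives women who did complete an OGTT no rule at 6 and 12 months.

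**Table 3 is a routine schedule.** Tests triggered by a result would not normally appear in it, and saying that OGTT values will be used most naturally means that one is obtained. This is fair: the empty cells are not an error in themselves, and reading A is the more natural one. The conflict at HbA1c 6.7 with fasting glucose 130 remains under that reading.

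**The counts are not effect sizes.** This stands. They show where the rules part, on values chosen for illustration, and the 2 of 4 depends on which repeat test is picked.

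**The side points are weak.** Exclusion criterion 13 concerns the first trimester and cannot show which rule governs later; it only shows that 6.5 is used elsewhere. The missing OGTT limit in Outcomes monitoring is a small matter, because 200 is the only 2-hour limit in the protocol.

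**Existing safeguards.** A physician reviews all laboratory results as they arrive, and participants receive their results after the 12-month visit. An unnoticed result is therefore unlikely, but the reviewing physician still has two written rules to choose between.

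**Conclusion.** The contradiction holds on the text alone. For HbA1c from 6.5 to 7.0 at 6 or 12 months, the two rules can differ in the action taken, the test that decides and the time of referral. The certain case is HbA1c in that range with fasting glucose above 126: Outcomes monitoring diagnoses at the visit, while the Table 3 note tests further first. With fasting glucose not above 126, the difference depends on whether the note is taken to order an OGTT and on which repeat test is used.

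The size is minor. The number of women in the range cannot be derived from the protocol. Diabetes incidence is not a primary or secondary outcome. Both parts keep women diagnosed after the 6-week visit in follow-up (the first note under Table 3 adds that their permission is asked), so the weight analysis and the power calculation do not depend on which limit is used. This is an internal inconsistency in a safety rule, and it should be corrected for that reason.

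**What to change.** State one rule, in the same words, in the Table 3 note and in Outcomes monitoring, and say that it applies to all participants at 6 and 12 months.

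- **Preferred:** fasting glucose above 126 or HbA1c 6.5 or higher triggers a repeat test. Delete the sentence that leaves 6.5 to 7.0 to the OGTT. Keep the 2-hour limit of 200 in the Table 3 note and add it to the 6- and 12-month bullet in Outcomes monitoring, for use when the repeat test is an OGTT. Move that bullet out from under the line for women without an OGTT.
- **Alternative, if the investigators want the OGTT to decide:** state in both places, and in a footnote to Table 3, that HbA1c from 6.5 to 7.0 at 6 or 12 months triggers an OGTT, with a 2-hour limit above 200, whether or not the woman had GDM.

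The choice between the two is clinical. The first is simpler and needs no added OGTT. It costs wording in two places and has no statistical cost. The second adds the footnote and one OGTT for each woman with an HbA1c in that range at either visit.
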